### Objectives

The primary objective of the Diabetes Risk Communication Trial (DRCT) is to assess whether communicating a genetic risk estimate for T2D in combination with standard lifestyle advice motivates greater changes in objectively measured physical activity than a phenotypic risk estimate for T2D in combination with standard lifestyle advice or standard lifestyle advice alone.

The secondary objectives are to determine the effects of the interventions on self-reported diet; self-reported weight; intentions to be physically active and to engage in a healthy diet; anxiety; diabetes-related worry; self-rated health; and other cognitive and emotional theory-based antecedents to behaviour change.

## Methods

### Study design

The DRCT is a parallel group, open randomised controlled trial with allocation of approximately 580 participants to one of three groups. Participants in each group receive standard lifestyle advice, which includes general information about T2D as well as information about how to reduce the risk of developing the disease. In addition to this information, one group receives a genetic risk estimate for T2D, while another group receives a phenotypic risk estimate (intervention groups). The remaining group of participants (control group) does not receive either of the risk estimates until after they have completed follow-up. The design of the trial and flow of participants are shown in Figure1.

**Figure 1 F1:**
[figure not shown]
The flow of participants through the Diabetes Risk Communication Trial.

### Recruitment

Participants are recruited from the Fenland Study, an on-going population-based, observational study investigating the influence of lifestyle and genetic factors on the development of diabetes, obesity, and other metabolic disorders [47]. Residents of Cambridgeshire, in the east of England, born between 1950 and 1975 are potentially eligible to participate in the Fenland Study and are excluded by their general practitioner if they have been diagnosed with diabetes or a terminal illness with a prognosis of less than one year. Additionally, they are excluded if they suffer from a psychotic illness, are pregnant or lactating, or if they are unable to walk unaided. Approximately 28% of those registered with participating general practices in the Cambridgeshire Primary Care Trust have enrolled in the Fenland Study (more than 8,000 participants). Fenland Study participants visit a study centre where they undergo a health assessment. Blood samples are taken for the genotyping of SNPs associated with T2D. At the end of the assessment, Fenland Study participants are fitted with a combined heart rate monitor and accelerometer (described in detail below), which they are instructed to wear continuously for six days and nights prior to returning it to the study centre.

Participants of the Fenland Study are invited to take part in the DRCT if they have given permission to be contacted regarding potential involvement in future studies. Furthermore, they must have provided sufficient data to calculate their genetic and phenotypic risk estimates for T2D (described in detail below), and have worn the combined heart rate monitor and accelerometer for three or more full days without experiencing a severe skin reaction. Lastly, the monitor must have recorded at least 36 hours of complete data. Fenland Study participants who fulfil the inclusion criteria are invited to take part in the DRCT in the order in which they completed their health assessment (median 1.76 years prior to being invited), beginning with the most recent first. Potential participants are mailed an invitation letter, a study brochure, a sample consent form, and a response form. Those interested in taking part are asked to complete the response form and to return it in the enclosed freepost reply envelope. In the event of non-response, a second mailing is sent approximately four weeks after the first. Responders are excluded from the DRCT if they have been diagnosed with diabetes or are actively participating in another study. The exclusion criteria are explicitly stated in both the invitation letter and the study brochure, and are assessed in the response form via self-report.

### Baseline assessment

All baseline information is collected prior to randomisation. Responders who are eligible to take part in the DRCT are sent a baseline instruction letter, a consent form, and a baseline questionnaire. The instruction letter asks responders to read and sign the consent form prior to completing the baseline questionnaire. They are then asked to return both documents in the enclosed freepost reply envelope. A reminder letter, along with a second consent form and baseline questionnaire, is sent if the first consent form and questionnaire are not returned within two weeks. The measures assessed in the baseline questionnaire are combined with several measures taken during the participants’ Fenland Study health assessment in order to create a comprehensive baseline characterisation of the study population.

### Randomisation, allocation concealment and blinding

In order to ensure equal allocation across the three trial groups, participants are allocated to one of the groups using a blocked randomisation procedure. A statistician without knowledge of participant characteristics created a computer-generated list comprised of blocks of six that contain two of each of the three trial groups per block in a random order. The randomisation list was incorporated into a computer program that members of the study coordination team use for enrolment and automated randomisation of participants. Allocation is concealed from the study coordination team, researchers, and participants until the interventions are assigned. It is not possible to blind participants to which intervention they receive. However, researchers assessing the baseline characteristics of participants and the primary outcome of the trial remain blinded to group assignment. Additionally, an independent, quality assured data-entry company undertakes all data entry unaware of group allocation.

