### Data management and quality assurance

Each participant is assigned a unique numeric identifier at the beginning of the Fenland Study so that they can be tracked without reference to personal information. A new identifier is assigned to participants enrolled in the DRCT, and a data manager uninvolved in data collection maintains a link to the corresponding Fenland Study identifier. All personal data are stored on an encrypted drive, and links to personal information are only available to the study coordination team. Consent forms and questionnaire data are stored in locked filing cabinets in secure Entacard − protected sites. Questionnaire data are double entered by an independent, quality assured data-entry company.

Trained personnel conduct the trial according to the standard operating procedures established by the MRC Epidemiology Unit and the principles of good clinical practice [92]. Standardised delivery of the interventions is assured by having one member of the study coordination team prepare the intervention materials using an automated computer program. A second member verifies that the intervention materials are correct prior to sending them to participants.

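### A constant block of six on one list, in an open trial enrolled by a team that learns past allocations, leaves concealment vulnerable; undisclosed, randomly varied blocks would cost almost nothing

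*Protocol article*

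**What the plan says.** Under Study design, the protocol article describes a "parallel group, open randomised controlled trial with allocation of approximately 580 participants to one of three groups". Under Randomisation, allocation concealment and blinding, a statistician with no knowledge of participant characteristics produced a "computer-generated list comprised of blocks of six that contain two of each of the three trial groups per block in a random order"; the stated reason for blocking is equal group sizes. The section continues: "The randomisation list was incorporated into a computer program that members of the study coordination team use for enrolment and automated randomisation of participants". No stratification factor and no variation in block size is described.

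The same section says: "Allocation is concealed from the study coordination team, researchers, and participants until the interventions are assigned". Those named as blinded are the "researchers assessing the baseline characteristics of participants and the primary outcome of the trial remain blinded to group assignment" and an external data-entry company. The coordination team is not among them. Under Data management and quality assurance, delivery is standardised by "having one member of the study coordination team prepare the intervention materials using an automated computer program", and a second member checks the materials before posting.

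Two statements limit the consequences. Under Recruitment, people are invited in a fixed order set by the date of their health assessment, and exclusions are self-reported on a mailed form. Under Baseline assessment: "All baseline information is collected prior to randomisation", with consent and the baseline questionnaire returned by post.

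**The concern.** Concealment has two parts: the list must be hidden, and the next assignment must not be deducible from earlier ones. The program serves the first. The second depends on the block design. With a constant block of six holding two of each arm, the last place in every block is determined by the five before it, and earlier places are often partly determined. Whoever sees the run of past allocations and knows the block size can work this out without opening the list.

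Here the trial is open, one sequence runs through all participants, and the team that enrols also handles materials that differ by arm. If such a person could also influence which waiting participant is entered next, the composition of the arms could be affected, knowingly or not. That would be selection bias, which concealment is meant to prevent.

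**Working it through.** **Base number.** The article gives no figure for predictability, so there is none to reproduce. The number it applies to, about 580 randomised, can be checked from the Sample size section: SD 15.4, baseline to follow-up correlation 0.69, difference 4.1 kJ/kg/day, significance level 1.67% (taken as two-sided), power 80%.

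- SD after baseline adjustment: 15.4 × √(1 − 0.69²) = 11.15.
- Per arm: 2 × (2.39 + 0.84)² × 11.15² / 4.1², which rounds up to 155. Three arms: 465, as stated.
- Attrition of 20%: 465 / 0.80 = 581, against the stated figure of about 580.

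**Assumption for the rest.** The observer knows the block size, knows where each block starts and has tracked every earlier allocation. The article states none of these, so the results are upper bounds.

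**Orderings.** A block with two of each of three arms has 6! / (2! × 2! × 2!) = 90 equally likely orderings.

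**Allocations known with certainty** (only one arm left in the block):
- Places 1 to 4: never.
- Place 5: known when the last two places are the same arm. That is 3 × 6 = 18 of 90 orderings, or 0.2.
- Place 6: always, 1.0.
- Share: (0.2 + 1.0) / 6 = 20.0%. Of 580: 116.

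**At least one arm ruled out:**
- Places 1 and 2: 0.
- Place 3: the first two are the same arm, 18/90 = 0.2.
- Place 4: the first three are not all different, 1 − 36/90 = 0.6.
- Places 5 and 6: always, 1.0 each.
- Share: (0.2 + 0.6 + 1.0 + 1.0) / 6 = 46.7%. Of 580: about 271. This includes the 20% known with certainty; in the other 26.7% two arms remain possible.

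**Best-guess success** (always guessing the arm with most places left): (0.333 + 0.400 + 0.500 + 0.533 + 0.600 + 1.000) / 6 = 56.1%, against 33.3% by chance.

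**Other constant sizes, same assumption.** The share known with certainty is 33.3% for blocks of 3, 14.3% for 9 and 11.1% for 12. Larger constant blocks reduce the problem without removing it. Varying the size without disclosure works differently: the observer can no longer locate block ends reliably.

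**The case against.** The strongest reply is that the figures are conditional. Nothing in the article says that enrolling staff knew the block size, and its appearance in a published article does not show that they did. The list sits inside a program that randomises automatically. The member who prepares materials and the one who checks them are not said to be the members who enrol, nor to work through participants in sequence. This stands: 20%, 47% and 56% are ceilings.

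A reader might infer that the stated concealment does not hold, or that about 116 allocations were known in advance. The documents do not support either reading. They show a method open to deduction under certain knowledge, not that anyone had or used it. A reader might also infer that the same staff hold the returned packs and choose the order of entry. The article says only that packs come back by post. It does not say who holds them or how their order is set.

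The usual routes to selection are also mostly closed: invitation order is fixed, exclusions are self-reported by post, and consent and baseline data precede randomisation. The outcome is monitor-measured, its assessors are blinded, and the analysis is by intention to treat with baseline adjustment. This stands too, and is why the likely bias is small.

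Finally, it can be said that whether block size was withheld, and how entry order was set, are details an article may leave to the full protocol. That is fair for the missing details. It does not answer the point about the method that is stated: constant blocks on one list, when varied blocks would serve the same aim of equal groups with better protection.

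**Conclusion.** The point holds as an inexpensive improvement to a stated design choice. Constant blocks of six on one list, in an open trial whose enrolling team learns past allocations, make concealment vulnerable. At most 20% of allocations (about 116 of 580) could be foreseen with certainty, and at most 47% (about 271) with at least one arm excluded. Both ceilings require knowledge of the block size, the block starts and the full sequence. They also assume a single unstratified list, as the article describes.

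No failure of concealment and no bias in any estimate is shown. The one remaining opening is the order in which people who have already consented and returned their packs are entered. The sample size does not depend on this point.

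**What to change.** For participants not yet randomised:

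1. Have the independent statistician replace the rest of the list with blocks of randomly varied size in multiples of three, with the sizes not disclosed to the coordination team.
2. Have the program randomise in the order in which consent form and baseline questionnaire are received, so that staff cannot alter the queue.
3. State whether the present block size was withheld from the coordination team and how entry order has been set so far. If randomisation is already complete, this statement is all that can be added.

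The cost is a small change to the randomisation program, with retesting, and a short amendment. No extra participants are needed. An unfinished final block could leave the arms unequal by a few participants, which matters little at about 193 per arm (580 / 3).

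Simple randomisation is not recommended. The SD of the difference between two arm sizes would be √(580 × 2/3) = 19.7, so differences of up to about 39 (1.96 × 19.7) would fall within the usual 95% range. That gives up the article's stated aim of equal allocation, which varied blocks keep.

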### Intervention

The interventions consist of either a genetic risk estimate or a phenotypic risk estimate for T2D, both in combination with standard lifestyle advice (see Appendices A through C for examples). Several modes of intervention delivery were considered, including face-to-face counselling, telephone conversations, and printed materials. Printed materials were chosen as they have the advantage of being simple, inexpensive, and do not create any undue burden for participants in relation to time and travel. Both interventions contain information presented in a manner similar to that of several direct-to-consumer genetic testing companies (e.g., http://www.navigenics.comhttp://www.decodeme.com, and http://www.23andme.com), and they were designed to incorporate evidence regarding the most effective methods for communicating disease risk estimates. As it remains unclear whether an individual’s understanding of risk is more accurate after the provision of a numerical risk estimate or a verbal risk estimate [34,48], both the genetic and phenotypic risk estimates include a numerical (i.e., percentage) and verbal estimation of risk (i.e., “below average”, “average”, or “above average”). Moreover, research suggests that comparative risk estimates may have a greater influence on behaviour than absolute risk estimates [49,50], and that visual representations of risk elicit greater recall and understanding of risk [33,34,51]. Thus, estimates are framed in comparison to the average risk within each participant’s age and sex specific group, and participants are told what percentage of Fenland Study participants have a risk estimate higher, lower, and equal to their own. Each piece of information is represented using a visual image.

#### Genetic risk estimate

Trained personnel at a study centre took blood samples during the Fenland Study. Genomic DNA was extracted from up to 7.5 ml of whole blood stabilised in EDTA using an Autopure LS DNA preparation platform (Qiagen, Crawley, UK). Genotyping was carried out by the Department of Pathology, University of Cambridge using the HumanCardio-Metabo Beadchip Kit supplied by Illumina® (Cambridge, UK). The following 23 SNPs were identified through adequately powered genome-wide association studies, the associations with T2D reached the genome-wide significance level (p-values for associations less than 5x10^-8^), and the associations were replicated in at least one independently published study: CDKN2A/B *rs10811661*, MTNR1B *rs10830963*, HHEX *rs1111875*, ZFAND6 *rs11634397*, ADCY5 *rs11708067,* SLC30A8 *rs13266634*, CENDT2 *rs1552224,* DGKB/TMEM195 *rs2191349,* KCNQ1 *rs231362,* ADAM30 *rs2641348,* PROX1 *rs340874,* IGF2BP2 *rs4402960*, ADAMTS9 *rs4607103,* ZBED3 *rs4457053,* CDKN2A/B *rs564398,* NOTCH2 *rs10923931,* IRS1 *rs7578326,* CDKAL1 *rs7756992,* GCKR *rs780094,* TCF7L2 *rs7903146,* JAZF1 *rs864745,* TP53INP1 *rs896854,* and VEGFA *rs9472138*[6-12]. All SNPs were in Hardy-Weinberg equilibrium (*χ*2, P > 0.05). Occasionally, one or more may have been missing due to random error in the genotyping process. In these cases, linkage disequilibrium was taken advantage of in order to impute the genotype at the loci for which data were missing. The odds ratio for each SNP included in the estimation of genetic risk was taken from replication samples, and the allele frequency was taken from the HapMap population.

The genetic risk estimate is presented as an estimate of the participant’s lifetime risk of developing T2D. It was calculated using the aforementioned genetic data and procedures outlined in literature published by several direct-to-consumer genetic testing companies (see Appendix D for an example) [52-54]. First, assuming a multiplicative model, the odds ratio for the risk allele of each SNP associated with T2D and the corresponding population frequency of the risk allele were used to determine the odds ratios and frequencies of the three possible genotypes at each locus. Next, the average population risk at each locus, relative to the no risk genotype, was calculated by summing the product of the genotype specific odds ratios and frequencies. Each genotype specific odds ratio was then divided by the average population risk at each locus in order to derive an estimate of the genotype specific risk that is relative to the average population risk at each locus. The genotype specific risks were then combined using a multiplicative model to create a total genetic risk relative to the population for each participant. Lastly, the participant’s total genetic risk was multiplied by their corresponding age and sex specific T2D residual lifetime risk estimate [55].

#### Phenotypic risk estimate

Age, sex, family history of diabetes, smoking status, and prescription of steroid or anti-hypertensive medication were assessed through self-report during the Fenland Study. Height and weight were also measured using standardised procedures [47], and body mass index was calculated as weight (kg) divided by the square of height (m) [56].

The phenotypic risk estimate is presented as an estimate of the participant’s lifetime risk of developing T2D. It was calculated using the aforementioned phenotypic data and the Cambridge Diabetes Risk Score [57], which has been previously validated in the EPIC-Norfolk study, where it was shown to provide good prediction of incident T2D (area under the receiver operating characteristic curve equal to 0.75) [58]. First, each participant’s T2D risk score was calculated (from 0 to 1) using the published beta-coefficients from the Cambridge Diabetes Risk Score. Next, the natural logarithm of the score was taken and the results were stratified into age and sex specific groups. Lastly, the percentage difference from the mean was calculated for each participant and the resulting percentage was multiplied by their corresponding age and sex specific T2D residual lifetime risk estimate [55]. Calculating the phenotypic risk estimates in this way generated values that were broadly similar to the genetic risk estimates.

#### Standard lifestyle advice

All participants receive general information about T2D irrespective of risk and group assignment. The information includes a brief description of T2D and an explanation of the risk factors, symptoms, diagnosis, treatment, and consequences of the disease. All participants are told that the likelihood of developing the disease can be reduced by following physical activity and dietary guidelines. They are equally encouraged to maintain a healthy weight and to follow government recommendations to engage in at least 30 minutes of moderate intensity physical activity on five or more days of the week [59] and to eat five servings of fruit and vegetables a day [60].

### Immediate post-intervention assessment

Following allocation to a trial group, participants are mailed an intervention instruction letter, standard lifestyle advice along with the relevant intervention materials, and an immediate post-intervention questionnaire. The instruction letter asks participants to read through the intervention materials until they feel happy that they understand them, complete the immediate post-intervention questionnaire, and return it in the enclosed freepost reply envelope. A reminder letter, along with a second copy of the questionnaire, is sent if the first is not returned within two weeks. If the questionnaire is still not returned after four weeks, a second reminder letter is sent.

### Follow-up assessment

Approximately eight weeks post-intervention, participants are sent a follow-up instruction letter, a combined heart rate monitor and accelerometer, and follow-up questionnaires. A member of the study team contacts each participant by telephone approximately one week before the monitor is due to be posted to check that it is a convenient time for them to wear it. If it is an inconvenient time, an alternative time is arranged. The instruction letter asks participants to wear the monitor for six days and nights continuously, and then return it along with the follow-up questionnaires in the enclosed Special Delivery freepost reply envelope. A reminder letter is sent if responses are not received within two weeks. If responses are still not received after three weeks, a member of the study team contacts the participant by telephone to arrange for the monitor to be returned. If necessary, a second telephone call is made. Upon receipt of the monitor and questionnaires, participants are mailed a study completion letter and a wait-list response form. The response form asks participants to indicate if they would like to be sent whichever risk estimate(s) they have not yet received, and indicates that we will send feedback about their current physical activity level shortly. They are asked to return the response form in the enclosed freepost reply envelope. If a response is not received within two weeks, we send only the physical activity feedback.

